### Blinding

Acupuncturists cannot be blinded as they will be required to apply the various stimulation methods to intervene. However, there will be blinded of group assignments among the participants, because the acupuncture needles are the same, and the diclofenac diethylammon gel and placebo gel are identical in appearance. In addition, participants will be arranged in different rooms for treatment, in order to prevent them from communicating with each other to understand their treatment programs, and the acupuncturists will not communicate any information to participants about their treatment programs. Group assignments will be concealed from outcome assessor and data analysts. Only after data analysis, we will perform unblinding analysis. In the data summary stage, the three separation principles of researcher, operator, and statisticians will be implemented.

### Researchers

These three groups of participants will be treated by acupuncturists registered with China’s Ministry of Health which have over 6 years of clinical experience. Moreover, the data collectors and analysts who are not aware of the random assignment protocol will monitor all phases of the trial. All researchers will receive rigorous training about project objectives and standard procedures before the start of the trial, including those responsible for recruiting test participants, outcome assessor, acupuncturists, and statisticians.

### Safety assessment

During the trial, adverse events (AEs) will be documented by using safety assessments, which include date, extent, frequency, and duration of AEs. The most common AEs related to acupuncture in this trial were pain, bleeding, hematomas, fainting, or other severe events. Moreover, redness, swelling, and itching of the skin are the AEs associated with diclofenac diethylammon gel. In the event of adverse events, emergency measures will be taken and documented in detail in the CRF. In the event of severe adverse events, the research ethics committee will determine whether the participant should be withdrawn from the study. Patients may withdraw from this trial if any AEs occur.

### Interventions

This trial is divided into three groups: Group A: verum acupuncture group (verum acupuncture and placebo gel), Group B: diclofenac diethylammon group (diclofenac diethylammon and sham acupuncture), and Group C: placebo group (sham acupuncture and placebo gel). Aside from the experimental scheme, patients will be advised not to use other any methods for the treatment of KOA. At the beginning of the trial, all licensed acupuncturists, who have at least 6 years of experience in acupuncture, will be trained in the clinical operation organized by the research group.

### Group A

Subjects in verum group will be treated with verum acupuncture and placebo gel for 4 weeks. We will determine the locations of the acupoints using the nomenclature and locations of acupuncture points specified in the National Standard of the People's Republic of China (GB/T 12346-2006) including SP9 (Yinlingquan), GB34 (Yanglingquan), EX-LE4 (Neixiyan), and ST35 (Dubi) (Table 2 and Fig. 2). Furthermore, two Ashi acupoints (where the patient feels the most pain) will be added based on patients condition.

**Table 2 Tab2:** Locations of acupoints for Group A

Acupoint	Location
SP9	On the tibial aspect of the leg, in the depression between the inferior border of the medial condyle of the tibia and the medial border of the tibia
GB34	On the fibular aspect of the leg, in the depression anterior and distal to the head of the fibula
EX-LE4	On the anterior aspect of the knee, in the depression medial to the patellar ligament
ST35	On the anterior aspect of the knee, in the depression lateral to the patellar ligament

**Fig. 2 Fig2:**
[figure not shown]
The picture of acupuncture points

During acupuncture, the patient lies supine in a comfortable position, while the acupuncturist will sterilize the patient's skin with 75% alcohol and then use sterile needles (0.25 mm in diameter, 40 mm in length, Huatuo, Suzhou, China) to the acupoints, a depth of which is 21–26 mm. In order to generate "deqi," all needles will undergo manipulations of twirling and lifting, using a reinforcing-reducing method. The "*deqi*" refers to after the acupuncture is inserted into the acupoints, the patients may feel numbness, soreness, and heaviness, after manual manipulation or needle retention for a long time which are believed to be one of the key factors in the acupuncture efficacy. After that, the stimulation operation is performed every 10 min to maintain the *deqi* sensation, and each treatment lasts for 30 min. The verum acupuncture treatment will be continued for 4 weeks, 5 times a week, with 2 days of rest in between each week.

Placebo gel is manufactured by the Pharmacy Department of the First Affiliated Hospital of Henan University of Chinese Medicine. Its ingredients are white gel matrix, without any therapeutic effect, but it is the same as diclofenac diethylammon gel in appearance and texture. It will be applied to the surface of each affected knee three times a day for 5 consecutive days and for 4 consecutive weeks.

### Group B

In the diclofenac diethylammon group, the subjects will be treated with diclofenac diethylammon gel and sham acupuncture for 4 weeks. Diclofenac diethylammon gel (approval number H19990291, manufactured by Novartis Pharmaceutical Co., Ltd., Beijing, China, specification: 20 g. Each gram of gel contains 10 mg of diclofenac diethylammon) will be applied to the surface of each affected knee three times a day for 5 consecutive days for 4 consecutive weeks.

The acupoints for sham acupuncture will select six non-acupuncture points that are separate from traditional acupuncture or meridians. The non-acupoints are shown in Table 3 and Fig. 2. The acupuncture procedure will be the same as Group A, but in order to avoid deqi sensations as much as possible, the needle depth is 1–2 mm and do not have any manipulation, directly retained for 30 min. The sham acupuncture treatment will also last 4 weeks, 5 times a week, with 2 days of rest in between each week.

**Table 3 Tab3:** Locations of non-acupoints for Groups B and C

Non-acupoint	Location
NA1	Located between ST35 and gallbladder meridian, on the same level as ST35
NA2	Located between EX-LE4 and spleen meridian, on the same level as EX-LE4
NA3	3 cun* below GB34 (between the gallbladder and bladder meridian)
NA4	3 cun* below SP9 (between the spleen and kidney meridian)
NA5	On the anterior aspect of the thigh, 5 cun above the upper edge of the patella (between the spleen and stomach meridian)
NA6	On the anterior aspect of the thigh, 4 cun above the upper edge of the patella (between the spleen and stomach meridian)

*1 cun (≈ 20 mm) is defined as the width of the interphalangeal joint of the patient’s thumb

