### Double-dummy design can effectively improve the experimental design quality

Double dummy is a common technique in clinical trials. In clinical trials, when the two treatments are inconsistent in appearance or pathway, a placebo is prepared for each treatment group and control group in order to achieve blinding and thus the treatment group and the control group in the appearance or approach to maintain the same treatment. Double-dummy technology is used to realize the blind method, and the acupuncture clinical research model with acupuncture therapy and medicine as control can be formed, which can improve the quality of acupuncture clinical trials. At present, some studies also have adopted the double-dummy design in the treatment of acupuncture for migraine and insomnia, which achieved the purpose of double-dummy patients by designing verum acupuncture and placebo versus sham acupuncture and true medicine [43, 44]. In this study, according to the double-dummy design, all three groups will receive verum/sham acupuncture combined with diclofenac diethylammon/placebo gel treatment. In order to minimize the potential therapeutic effect and gain high patient trust from patients, we will carefully take into consideration the choice of sham acupuncture and placebo.

However, it is difficult to design an inert placebo control for acupuncture since it is a physical intervention. Currently, acupuncture at ineffective acupoints or non-effective acupuncture at effective acupoints is used in KOA clinical trials as a placebo-controlled approach. It is possible, however, that these approaches may result in a wide range of physiological responses [45, 46]. Therefore, our placebo acupuncture method will consist of non-effective acupoints with the non-effective puncture at the local of the knee as the placebo acupuncture. Moreover, after needle insertion, acupuncturists will be requested not to perform any further manipulation to avoid deqi sensation and minimize the possible effects of sham acupuncture. In addition, the placebo gel is identical in appearance, odor, dosage, color, and texture to the diclofenac diethylammon gel, but has no other substance that might affect efficacy assessments.

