### The selection of acupoint and non-acupoint is reasonable

As we know, acupoints can treat diseases in the local and surrounding areas where they are located [47]. In this trial, four acupoints around the knee joint will be used for verum acupuncture, including SP9, GB34, EX-LE5, and ST35, which are mostly located around knee joint on ligaments and tendons. At the same time, two *Ashi* acupoints will be selected according to the syndrome type to fulfill the needs for individualized treatment, which are effective in relieving local pain.

In sham acupuncture, six non-acupoints are also selected around the knee joint. These non-acupoints are separate from conventional acupoints or meridians, which may allow patients receiving sham acupuncture to overcome psychological bias.

In this trial, we will set a standardized acupuncture treatment program and manipulation, which purpose is to evaluate the therapeutic effects of acupuncture, a drug, and a placebo on KOA. As a result of the completion of this trial, evidence for acupuncture to relieve pain and improve physical function in KOA patients can be provided, as well as a reference for the clinical application of acupuncture treatment of KOA.

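### Verum needles are re-stimulated every 10 minutes while sham needles are left in place for 30 minutes with no matching contact described, so A–C and A–B differences include unequal therapist attention

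*Protocol article*

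**What the plan says.** **Verum (Group A).** After insertion, "all needles will undergo manipulations of twirling and lifting, using a reinforcing-reducing method", with the aim of producing deqi. Then "the stimulation operation is performed every 10 min to maintain the" deqi sensation, in a session of 30 minutes.

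**Sham (Groups B and C).** The Group B section says "The acupuncture procedure will be the same as Group A, but in order to avoid deqi sensations as much as possible", and continues that "the needle depth is 1–2 mm and do not have any manipulation, directly retained for 30 min". The Group C section adopts the Group B sham unchanged. The Discussion repeats that nothing is done to the sham needles after insertion, so as to avoid deqi and keep the sham as inert as possible.

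**Sessions.** Study design gives 20 sessions over weeks 1 to 4. Under the discontinuation criteria a participant may miss up to 4 of them and stay in the trial.

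**Blinding.** The Blinding section says acupuncturists cannot be blinded. For participants it relies on needles that are the same, gels of identical appearance, separate treatment rooms, and acupuncturists who disclose nothing about the treatment. The Discussion describes the purpose of a double dummy as enabling "the treatment group and the control group in the appearance or approach to maintain the same treatment".

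**The concern.** A sham control should remove everything except the component under test. Here that component is needling at acupoints, at depth, with deqi. In Group A it comes with scheduled returns of the therapist to handle the needles. In Groups B and C no such returns are described. Attention and touch can change how patients report pain and function, and here they occur in one arm only.

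Three features of the protocol leave this unguarded:

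- The person giving the extra contact knows the allocation.
- The primary outcome is a questionnaire on pain, stiffness and function, and the VAS is marked by the patient. A blinded assessor does not protect such answers from an attention effect.
- The Credibility/Expectancy Questionnaire is given once, at baseline, so it cannot show whether the groups drift apart because of what happens in the sessions.

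The contrasts at stake are the ones the trial exists to estimate: acupuncture against placebo and acupuncture against diclofenac gel. All of Group A gets the extra contact and nobody else does, so no analysis of the trial data can separate it from the needling effect.

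**Working it through.** **1. The sessions side by side**

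| Feature | Group A | Groups B and C |
|---|---|---|
| Skin preparation, insertion, 30-minute session | yes | yes (stated to be as in Group A) |
| Manipulation after insertion | all needles | none |
| Re-stimulation during retention | every 10 min | none |
| Other therapist contact during retention | not described | not described |

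The second and third rows are stated procedures, not detail lost in condensing an article. The second is the intended difference. The third contains both the intended stimulation and an accompanying bedside visit.

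**2. Number of extra contacts**

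- Per session: returns at 10 and 20 minutes = 2. A stimulation at 30 minutes would coincide with the end of the session and is not counted.
- Over the course: 2 × 20 = 40.
- With the permitted 4 missed sessions: 2 × (20 − 4) = 32.

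**3. Which contrasts are affected**

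A–C and A–B each compare a group with the extra contact to one without it. B–C compares two groups given the same sham, so the contact cancels.

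**4. The plan's own sample size**

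Inputs from the Sample size section: reductions of 17, 13 and 10 WOMAC points, SD 10.24, two-sided 0.05.

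- One-way ANOVA, noncentrality λ = n Σ(mean − grand mean)² / SD².
- Grand mean 40/3 = 13.33. Sum of squared deviations 13.44 + 0.11 + 11.11 = 24.67.
- For n = 42: λ = 42 × 24.67 / 104.86 = 9.88, with 2 and 123 degrees of freedom. Power is 80.0%; for n = 41 it is 79.0%.

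The stated 42 per group is reproduced. The planned A–C gap is 17 − 10 = 7 points.

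**5. What an attention effect could do (illustration only)**

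Assume the extra contact alone lowers WOMAC by b points, and that needling has no specific effect. The value of b is not in the document. For a two-sided t-test of A against C with 42 per group:

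- Standard error = 10.24 × √(2/42) = 2.235.
- Noncentrality = b / 2.235, with 82 degrees of freedom.

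| b (assumed) | Noncentrality | Chance of p < 0.05 |
|---|---|---|
| 1 | 0.45 | 7% |
| 2 | 0.89 | 14% |
| 3 | 1.34 | 26% |
| 4 | 1.79 | 42% |

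The nominal rate is 5%. The table shows that a small attention effect would matter at this sample size. It does not show that such an effect exists or how large it is.

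**The case against.** **The difference is the treatment.** The protocol calls deqi a key factor in efficacy, gives re-stimulation the purpose of maintaining it, and explains why the sham omits it. This is a reasoned and disclosed choice of control, and it stands: stimulation need not be equalised. It does not cover the bedside visit, which can be matched without touching the stimulation.

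**Silence is not absence.** The sham procedure is otherwise the same as in Group A, and needles left in place do not rule out someone looking in on the patient. That may be settled in training or a fuller protocol. This stands in part: no matching contact is described, but it is not shown that there is none. A reader might infer that sham patients are left untouched. The text does not support that, since skin preparation and insertion take place in every group.

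**Ashi points.** A reader might infer that Group A patients are palpated for tender points at every session. The Group A section says "two Ashi acupoints (where the patient feels the most pain) will be added based on patients condition", without saying how the points are found or whether they are sought again each time. The Discussion says that the Ashi "acupoints will be selected according to the syndrome type to fulfill the needs for individualized treatment". Palpation and repeated examinations are therefore not in the document, and this point does not rest on them. Having sham patients palpated at painful spots would also be unwise: it could make the sham less inert, or create a new imbalance if Group A is not palpated.

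**Blinding.** Separate rooms mean that patients have no direct comparison, and the different sensations from depth and deqi would remain whatever is done about contact. Both statements are correct. Matching contact reduces one source of bias; it does not secure blinding.

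**The double-dummy sentence.** It is a general definition, not a promise of identical needle handling. It is fair to read it as the aim, but not as a contradiction.

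**Conclusion.** The point holds in a limited form. The protocol schedules about 2 returns per session in Group A, about 40 over the full course, and describes no equivalent contact in Groups B and C. An A–C or A–B difference on WOMAC or VAS therefore cannot be credited wholly to needling. B–C is not affected.

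A reader might go further and say that an advantage for Group A could not be credited to acupuncture at all. That does not follow: an unknown share may be non-specific, and that share may be small. Nor can the share be put as a percentage of the planned 7-point gap, because any such figure is only an assumed attention effect divided by 7.

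The conclusion assumes that each re-stimulation is carried out at the bedside and that no equivalent visit is made to sham patients under a procedure not shown here. It is a worthwhile, inexpensive improvement to the design, not an error that invalidates it.

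**What to change.** State in the Group B and Group C sections that the acupuncturist returns at the same 10-minute intervals as in Group A, for the same length of time, to check the needles without twirling, lifting or deepening them. Use one interaction script in all three groups. Points, needle depth, verum manipulation and the session schedule stay as they are, so the aim of avoiding deqi in the sham is kept. If such visits are already part of the operating procedure, a sentence saying so is enough.

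**Cost.** A few minutes of existing acupuncturist time per sham session, and an item in the training already planned; no extra staff. The check could cause slight sensation, which is limited by not stimulating the needle. Differences in sensation from depth and deqi will remain and should be acknowledged as a limitation.

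The change works only for sessions still to come. For any already delivered without it, the report should describe the unequal contact when interpreting A–C and A–B.

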### Group C

In the placebo group, subjects will be treated with sham acupuncture and placebo gel for 4 weeks. Sham acupuncture treatment procedure is the same as in Group B, and placebo gel will apply the same gel as in Group A.

### Outcome assessments

Outcome assessments were performed only on a knee that meets the inclusion criteria; when both knees meet the inclusion criteria, the more painful knee will be assessed.

### Primary outcome

The Western Ontario and McMaster Universities Osteoarthritis Index (WOMAC) [34] will be the primary outcome measure for this trial. The WOMAC is an osteoarthritis questionnaire with high reliability and validity that has been widely used in various clinical trials involving KOA patients [35]. WOMAC includes 5 pain-related items, 2 stiffness-related items, and 17 physical function-related items, each item is scored on a scale of 0–10, and the total score is on a scale of 0–240, with higher scores indicating more severe KOA symptoms in patients [36]. Outcome assessor will assess participants at baseline, week 4, week 8 and week 12, but the primary outcome will be the assessment at week 4.

### Secondary outcomes

The WOMAC subscale (pain, stiffness, and physical function) at baseline, week 4, week 8, and week 12 and the total WOMAC scores at week 4 and week 8 will be used as secondary outcome indicators.Pain visual analog scale (VAS) [37]: Using a 100-mm horizontal line anchored by two descriptors, patients will determine the most relevant point for quantifying their pain intensity: a score of 0 represents “no pain” and a score of 100 represents “severe pain.” After randomization, VAS will be collected at baseline, week 4, week 8, and week 12.Arthritis Quality of Life Measurement Scale Simplified Scale (AIMS2-SF) [38] includes five dimensions of physical function, pain symptoms, influence, social interaction, and role components, with a total of 26 items, a scale of 1–5 is applied to each item, and the sum of all five dimensions represents the total score. After randomization, the AIMS2-SF will be collected at baseline, week 4, week 8, and week 12.Credibility/Expectancy Questionnaire [39] is a measure of treatment expectations and reasonable confidence for use in clinical outcome studies and it is only assessed once at the baseline.Emotional Monitoring: Patients with KOA are often accompanied by symptoms of anxiety and depression. In this trial, patients' emotional states will be assessed using the Beck Anxiety Inventory (BAI) [40] and Beck Depression Inventory (BDI) [41]. After randomization, BAI and BDI will be collected at baseline, week 4, week 8, and week 12.

### Data collecting and monitoring

In this trial, all participants' data will be managed in the CRF both on paper and electronically. In order to ensure consistency of source data, all scales will be assessed by the same outcome assessor. Two researchers will independently enter the data into the EPIDATA electronic database to ensure accuracy. The Center for Evidence-Based Medicine will monitor the study and data every 3 months [42].

### Statistical analysis

The statistical analysis procedure of this trial will be performed using SPSS 22.0 software (IBM Corporation, Armonk, NY, USA). Statisticians responsible for data analysis will be independent of the research team and blind to the test settings. The data will be tested for normality using the quantile–quantile plots. We will analyze the data from WOMAC, VAS, AIMS2-SF, BAI, and BDI within the group and use paired-sample t-tests for those data that follow normal distributions, and in the case of data that did not conform to the normal distribution, Wilcoxon test will be used. Age, height, weight, and outcome assessments will be compared among the three groups, the one-way analysis of variance (ANOVA) will be applied to data conforming to a normal distribution, and the Kruskal–Wallis one-way ANOVA will be used to analyze data that do not follow a normal distribution. Intention-to-treat analysis will be used for outcome measurements to analyze missing values, based on the last observation carried forward method. In the analysis of missing values, only patients who attended at least 80% of the sessions and completed the follow-up in the allocated intervention group will be included. In addition, data will be tested by bilateral tests, and the confidence intervals are all 95% bilateral; *p* < 0.05 (*α* = 0.05) is considered to indicate statistical significance.

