### Inclusion criteria

The inclusion criteria are as follows: (1) adults aged 45–75 years, including the age of 45 and 75, male or female; (2)patients must fulfill the standard diagnosis of KOA established by the ACR; (3) radiologic confirmation of KOA [31] (Kellgren–Lawrence grades I to III); (4) VAS score ≥ 40 mm; (5) symptoms of knee bone friction sound during activity, pain, and morning stiffness ≤ 30 min have been present for over 6 months; and (6) participants fully understand this trial and written informed consent is signed.

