### Sample size

Power Analysis and Sample Size (PASS, provided by Shanghai Datanine Software Co., Ltd., China) was used for sample size calculation. Based on prior studies and clinical experience, we expected the WOMAC total score to decrease by 17 points after acupuncture, a reduction by 13 points after diclofenac diethylammon gel, and a reduction by 10 points in the placebo group [32, 33]; the standard deviation is 10.24. The type I error inflation can be avoided by setting the significance level at 0.05 on a two-sided basis. Forty-two participants in each group will have 80% power to detect significant differences between the groups. The sample size was increased to 46 participants in each group to supplement for a possible 10% loss at follow-up. So, this trial will include 138 participants in total.

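### Within-arm tests of change from baseline carry the same p < 0.05 rule as the between-group comparison, yet on the plan's own WOMAC figures the sham-plus-placebo arm is almost certain to pass

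*Protocol article*

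**What the plan says.** Two kinds of test are planned under Statistical analysis in the protocol article.

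- Within each arm: "We will analyze the data from WOMAC, VAS, AIMS2-SF, BAI, and BDI within the group and use paired-sample t-tests", with the Wilcoxon test as the fallback for non-normal data.
- Between arms: "outcome assessments will be compared among the three groups, the one-way analysis of variance (ANOVA) will be applied" to normal data, with Kruskal–Wallis otherwise.

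One closing rule covers both: "data will be tested by bilateral tests, and the confidence intervals are all 95% bilateral", with p < 0.05 counted as significant. The within-arm tests have no separate threshold and no descriptive label.

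The planning figures are under Sample size. For acupuncture, "we expected the WOMAC total score to decrease by 17 points after acupuncture"; for the gel, "a reduction by 13 points after diclofenac diethylammon gel"; and for sham plus placebo gel, "a reduction by 10 points in the placebo group". The SD is 10.24, with 42 per group for 80% power, raised to 46 for loss to follow-up. Under Inclusion criteria, entry requires "VAS score ≥ 40 mm".

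**The concern.** A test of change from baseline within one arm makes no use of the randomised control. The change it measures combines any treatment effect with placebo response, the natural course of the disease and regression to the mean. For pain, some regression to the mean is to be expected because patients must exceed a VAS threshold to enter. The plan itself expects the sham-plus-placebo arm to improve.

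A small p-value within the acupuncture arm is therefore expected whether or not acupuncture does more than sham. The stated between-group test is an omnibus test over three arms, so it does not say which arm differs. In the document as written, the paired tests are the only analyses that attach a p-value to a single arm. A report that acupuncture significantly improved WOMAC could rest on them alone. Significance in one arm and not in another could also be misread as a difference between those arms.

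**Working it through.** **Inputs** (Sample size section): expected falls in WOMAC total of 17 (acupuncture), 13 (diclofenac gel) and 10 (placebo); SD 10.24; two-sided α = 0.05; n = 42 per group. The document does not say whether 10.24 is the SD of change or of a single score. It is taken first as the SD of change, because it accompanies expected reductions.

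**1. Reproduce the plan's own figure.** For a one-way ANOVA the mean fall is (17 + 13 + 10)/3 = 13.33. The squared deviations are 13.44 + 0.11 + 11.11 = 24.67. The noncentrality is 42 × 24.67 / 10.24² = 9.88, on 2 and 123 degrees of freedom. Power is 80.03% at n = 42 and 78.98% at n = 41. The stated 42 per group is reproduced, so the inputs are read as the plan used them.

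**2. Paired t-test within each arm.** The standard error is 10.24/√42 = 1.580. The expected t is the mean fall divided by 1.580, and power comes from the noncentral t with 41 degrees of freedom.

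| Arm | Expected fall | Expected t | Probability of p < 0.05 |
|---|---|---|---|
| Sham + placebo gel | 10 | 6.33 | 99.999% |
| Diclofenac gel + sham | 13 | 8.23 | essentially 100% |
| Acupuncture + placebo gel | 17 | 10.76 | essentially 100% |

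With all 46 per arm, the placebo arm has t = 6.62 and a probability of 99.9997%.

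**3. Smallest significant mean change.** 2.0195 × 1.580 = 3.19 points, on a total score that runs from 0 to 240 (Primary outcome section).

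**4. No treatment effect at all.** If every arm fell by the placebo amount of 10 points, all three would be significant within arm in about 99.99% of trials (simulation, 20,000 trials, n = 42).

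**5. Contrast with the randomised comparisons.** On the same figures, two-sample t-tests at α = 0.05 have power of 87% (acupuncture vs placebo), 42% (acupuncture vs diclofenac) and 26% (diclofenac vs placebo). The diclofenac arm would thus pass its own baseline test almost surely, while its difference from placebo would be detected about one time in four.

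**6. Sensitivity for the placebo arm, n = 42.**
- If 10.24 is the SD of a single score, the SD of change is 10.24 × √(2(1 − ρ)), where ρ is the baseline-to-week-4 correlation. At ρ = 0 this is 14.48 and the probability is 99.2%. It is higher for any positive ρ.
- For assumed SDs of change that the document does not give:

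| Assumed SD of change | Probability of p < 0.05 |
|---|---|
| 15 | 98.8% |
| 20 | 88.6% |
| 25 | 71.6% |
| 30 | 55.9% |

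**7. Other scales.** The document gives no expected change or SD for VAS, AIMS2-SF, BAI or BDI, so no probability can be calculated for them.

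**The case against.** The best defence is that a paired t-test is a valid test of change from baseline and misleads only when read as a treatment effect. The plan does not announce that reading. Study design sets out to compare the three treatments, Sample size powers the trial for differences between groups, and Statistical analysis includes an among-group test. The p < 0.05 rule defines statistical significance, not efficacy. All of this stands, and it limits the point to an added analysis that is uninformative and open to misuse.

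The defence does not remove the point. The plan gives these p-values the same standing as the between-group ones, and the omnibus test supplies no arm-specific answer to set against them.

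A reader might infer more than the document supports:

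- *That efficacy will be concluded from the within-arm tests, or that they rank first because they are described first.* No sentence says so, and sentence order in a condensed article sets no hierarchy.
- *That all five scales will show significant improvement in every arm.* Planning figures exist for WOMAC total only. BAI and BDI have no entry threshold, so the regression-to-the-mean argument from the VAS criterion does not extend to them.
- *That the Discussion blames earlier trials for this practice.* It names inadequate blinding and control groups, not within-arm testing.
- *That a total number of such tests can be counted.* The Statistical analysis section does not say which visits or subscales enter the paired tests.

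**Conclusion.** The concern holds in a limited form. On the plan's own figures for WOMAC total, the sham-plus-placebo arm would be significant against its baseline with about 99.999% probability, or at least 99.2% if 10.24 is the SD of a single score. That near-certainty depends on the stated SD: with an assumed SD of change of 30 the probability falls to 55.9%. Even there a placebo arm passes more often than not, so the result cannot identify a working treatment. For the other four scales the conclusion rests on the logic of an uncontrolled comparison, not on a calculation.

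The among-group analysis and the sample size are unaffected. What is at stake is which statements about a single arm the plan permits, and the edit should be made.

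**What to change.** In the Statistical analysis section:

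1. Remove the within-group paired t-tests and Wilcoxon tests.
2. Report change from baseline in each arm as mean, SD and 95% CI, labelled as description and without p-values.
3. State that efficacy conclusions rest only on randomised between-group differences.

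The third step matters because a per-arm interval that excludes zero can be misread in the same way as a p-value.

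The cost is an edit to one section and slightly less analysis. Sample size, visits and data collection do not change. The Trial status section says recruitment had not begun at the time of writing; if the edit is made later, it should still precede unblinding. The downside is negligible, because the per-arm changes are still reported.
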